#### Other Assessments

Demographic information collected included sex, age, ethnicity, and current type of residence. Self-reported academic information collected included the degree type and the number of enrolled courses. Academic performance was evaluated based on students’ self-reported grades. Trained staff measured the participant’s anthropometrics and instructed participants to wear light clothing and remove their footwear. The body weight was measured using a calibrated digital scale (Health o meter Professional Remote Display, Sunbeam Products Inc) to the nearest 0.1 kg. Height was measured using a 235 Heightronic Digital Stadiometer (Quick Medical) to the nearest 0.1 cm. BMI was calculated and evaluated using previously defined categories [56]. Food security was assessed using a 6-question survey, as described by Entz et al [57].

Participants in the intervention group were asked to evaluate MVP at the week 12 visit using the Mobile App Rating Scale questionnaire [58]. Subscales for the following sections were calculated: engagement, functionality, esthetics, and information quality. To account for possible ratings of *not applicable*, the mean is calculated for each subscale and summed to generate a mean total score, where a higher total mean score represents a positive evaluation.

### Intervention Preference and Website Usage Data

System-obtained data were collected directly from the MVP for participants allocated to the intervention group. These data included information on the total number of log-ins, duration of activity, and usage of specific components of the app (ie, frequency of daily reflections, frequency of planned physical activities). A member of the study team reviewed participants’ platform usage every 3 weeks to assess the log-in activity. Individuals who had been identified as not logging on to the platform in that 3-week period were contacted by a member of the research team via email or over phone to ask if their ability to access the platform had been impeded and to act as a reminder of their agreement to use the platform as frequently as possible.

### Data Management

Study data were collected and managed using REDCap electronic data capture tools hosted at the University of Alberta [37,38]. REDCap is a secure, web-based software platform designed to support data capture for research studies, providing (1) an intuitive interface for validated data capture, (2) audit trails for tracking data manipulation and export procedures, (3) automated export procedures for seamless data downloads to common statistical packages, and (4) procedures for data integration and interoperability with external sources. Data collected using paper files at baseline and week 12 were transferred into REDCap and reviewed by an independent researcher within the team to identify data entry errors. At week 6, the study questionnaires were delivered electronically through REDCap and collected directly from the participant. Platform-obtained data were managed using Microsoft Excel (Microsoft Corporation).

### Statistical Analysis and Power and Sample Size Rationale

#### Statistical Analysis

Our analysis of the primary outcome will be based on an intention-to-treat analysis using inverse probability weighting. Our analysis of the secondary and exploratory outcomes will be based on per-protocol and intention-to-treat analyses using inverse probability weighting. The effects of intervention over time will also be investigated using a generalized estimating equation. SPSS 25 (IBM Corporation) statistical software will be used for the data analysis. Characteristic variables will be compared between the 2 treatment groups and between those that did and did not complete the study. Differential variables will be used as covariates in the statistical analyses. *P*<.05 will be considered statistically significant.

#### Power and Sample Size

The sample size was calculated using G-Power software (version 3.1.9.2, Heinrich-Heine-Universität Düsseldorf) [59] and based on the perceived stress scale scores of distressed adults after an internet-based stress management intervention [60]. With effect sizes of 0.74, a level of significance of 5%, and statistical power of 95% (power=1-β=0.95), the number of participants required is 33. With an anticipated attrition rate of 20%, we aimed to recruit 100 participants and have 80 participants complete the intervention.

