### Assessment of Study Outcomes

#### Primary Outcome

Our primary outcome is the difference in change over time in perceived stress (baseline to week 12) between the groups. Perceived stress was measured using the self-reported Stress Indicator Questionnaire [42]. Total scores range from 73 to 365 points, with higher total scores indicating higher levels of perceived stress.

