### Conclusions

Preventative self-care is important for first-year university students who may not have established this skill and are simultaneously experiencing new stress and pressures of postsecondary education. Targets were obtained for the sample size. This study will determine whether the web-based platform has a direct impact on health and wellness among first-year university students and could become an important tool for virtual, preventative self-care delivery.

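### The stated requirement of 33 participants for 95% power does not follow from the printed inputs and does not lead to the targets of 80 completers and 100 recruited

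*Protocol article*

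**What the plan says.** All the inputs are in one short paragraph of the protocol article, under Power and Sample Size:

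- **Effect size and alpha:** "With effect sizes of 0.74, a level of significance of 5" percent.
- **Power:** 95%.
- **Software:** G-Power 3.1.9.2. The test family is not named.
- **Result and targets:** "the number of participants required is 33. With an anticipated attrition rate of 20%, we aimed to recruit 100 participants", with 80 expected to complete.

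The paragraph does not say whether 33 is a total or a per-group number, whether the test is one- or two-sided, or whether a within-person correlation was assumed.

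The design that the figure has to serve is stated elsewhere in the article. Allocation is 1:1 to two arms (Screening, Randomization, and Treatment Allocation). The primary outcome is between-group: "Our primary outcome is the difference in change over time in perceived stress (baseline to week 12) between the groups". The Results section reports 80 completers, 35 in the intervention group and 45 in the control group. The Conclusions state: "Targets were obtained for the sample size".

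**The concern.** A printed requirement should follow from the inputs printed beside it. Here 33 looks too small for a two-group comparison at d = 0.74 with 95% power. The next step, from 33 with 20% attrition to 80 completers and 100 recruited, has no visible arithmetic behind it.

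What is at stake is how the primary result is read. A reader who takes the 95% at face value would treat a null result as having a 5% type II error at d = 0.74. If the error under the usual analysis is nearer 10%, or depends on assumptions that are not printed, the paper claims more than its calculation supports.

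**Working it through.** **Inputs.** From Power and Sample Size: d = 0.74, alpha = 0.05, power = 0.95, n = 33, attrition 20%, targets 80 and 100. From the randomization section: two arms, 1:1. From Results: 35 and 45 completers. Sidedness is not stated, so both are shown. I take 0.74 as a standardised mean difference.

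**Formula.** Two-sample t-test, exact noncentral t: df = n1 + n2 − 2 and noncentrality λ = d·√(n1·n2/(n1+n2)). Power is the probability that a noncentral t variable exceeds the critical value (in absolute value if two-sided).

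**Step 1: try to reproduce 33.**

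| Reading of 33 | λ | Power, two-sided | Power, one-sided |
|---|---|---|---|
| Total (16/17) | 0.74·√(272/33) = 2.12 | 53.9% | 66.7% |
| Per group (33/33) | 0.74·√16.5 = 3.01 | 84.1% | 90.8% |

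No reading reaches 95%. With 33 per group, the effect detectable at 95% power (two-sided) is d = 0.90.

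**Step 2: the n that the inputs require.**

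- Two-sided: 48 per group gives 94.8% and 49 gives 95.2%, so 49 per group (98 analysed). The normal approximation gives 48.
- One-sided: 40 per group gives 94.9% and 41 gives 95.3%, so 41 per group. The normal approximation gives 40.
- Other tests on the same inputs: a paired t-test needs 26 (two-sided) or 22 (one-sided); Mann-Whitney needs about 51 to 57 per group two-sided. Neither gives 33.

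**Step 3: what would produce 33 per group.** Each route needs an input that the article does not print:

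- ANCOVA, effective d = 0.74/√(1−r²): 33 per group at a baseline correlation of about 0.58.
- Change score with 0.74 in raw-score SD units, effective d = 0.74/√(2(1−r)): 33 per group at r of about 0.67.
- Repeated-measures between-factors F test with f = 0.37, three measurements and correlation 0.5: 66 in total.

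**Step 4: the attrition step.** Dividing by (1 − 0.20):

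- 33/0.8 = 41.25, so 42
- 66/0.8 = 82.5, so 83
- 80/0.8 = 100

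The last line is consistent in itself, but 80 does not come from 33 or 66 through 20% attrition. A 98-completer requirement would need 98/0.8 = 122.5, so 123 recruited.

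**Step 5: power with 80 completers at d = 0.74, unadjusted t-test.**

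| Split | Two-sided | One-sided |
|---|---|---|
| 40/40 | 90.5% | 94.9% |
| 35/45 | 90.0% | 94.6% |

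Smallest detectable effect at 35/45, two-sided: d = 0.64 at 80% power and d = 0.82 at 95%.

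**Step 6: sensitivity to correlation.** Change score, 0.74 in raw-score SD units, 35/45, two-sided. The correlation is my assumption; the article gives none.

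| r | Effective d | Power |
|---|---|---|
| 0.3 | 0.625 | 78% |
| 0.4 | 0.675 | 84% |
| 0.5 | 0.740 | 90% |
| 0.6 | 0.827 | 95% |
| 0.7 | 0.955 | 99% |

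**The case against.** The strongest reply is that about 90% is not a property of this design. It is the power of one analysis: unadjusted, two-sided, on completers. The Statistical Analysis section plans intention-to-treat with inverse probability weighting, allows covariates and adds a generalized estimating equation. It does not state sidedness. A one-sided test gives nearly 95% with 80 completers. If baseline stress were adjusted for, 95% would be reached at a correlation of about 0.44. Weighting could pull the other way and is not modelled here. All of this stands, so 90% has to be reported with its assumptions. It does not rescue 33, which fails both one- and two-sided on the printed inputs.

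A reader might go further in three ways that the documents do not support:

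- **That the authors powered a different test from their primary outcome.** The repeated-measures F test in Step 3 averages over visits and would fit that story. But ANCOVA and a change score also pass through 33 per group, and the change score is the stated primary outcome. Which calculation was run cannot be known from the article.
- **That the trial is badly underpowered.** The 80 completers exceed 2 × 33 = 66, and power at d = 0.74 is about 90% or better in most of the scenarios above.
- **That the effect size is wrong for this population, or that the recruitment claim is false.** The article openly says that the calculation was "based on the perceived stress scale scores of distressed adults after an internet-based stress management intervention". How well that transfers to first-year students on another instrument is a matter of judgement that cannot be settled here. The 80-completer target was met exactly; 97 randomised against an aim of 100 is a minor shortfall, openly stated.

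A fuller plan could supply the missing test or correlation. It could not make 33 follow from the inputs as printed.

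**Conclusion.** The point holds as an error of reporting and arithmetic. On the stated inputs the requirement is 49 per group two-sided or 41 one-sided, not 33. The number is not labelled as total or per group, and 20% attrition does not carry it to 80 and 100. The 95% power claim is therefore unsupported as written.

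Under an unadjusted two-sided t-test, 80 completers give about 90% power at d = 0.74, so the type II error is about 10% rather than 5%. That figure becomes about 95% one-sided, and runs from about 78% to 99% for a change score with correlations of 0.3 to 0.7. These results assume that 0.74 is a standardised mean difference and that only completers contribute outcome data. The conclusion is limited to a misreported rationale.

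**What to change.** Rewrite the Power and Sample Size paragraph so that a reader can reproduce it:

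1. Name the test, its sidedness and any correlation assumed, and say whether n is per group or in total.
2. Correct 33, or print the inputs that produce it, and derive the 80 and 100 targets from the result.
3. Replace the 95% claim with the power that 80 completers give at d = 0.74 under those assumptions. For an unadjusted two-sided two-sample t-test: about 90% (90.5% at 40/40, 90.0% at 35/45), with a smallest detectable d of about 0.64 at 80% power. Mark the 35/45 figure as based on achieved numbers, since it was not part of the prospective rationale.
4. Add that power would be about 95% if the test were one-sided, and about 78% to 99% for a change score with correlations of 0.3 to 0.7 when 0.74 is in raw-score SD units.

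Optional: comment on how far the effect-size source applies to this population and scale, and say in the Conclusions that the target met was the 80 completers.

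The cost is a text correction. No added enrolment and no change to the analysis are needed; the stated power becomes less favourable under the usual two-sided reading.

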## Results

Study recruitment began in August 2018. Batch recruitment was used for enrollment in the fall (September 2018 to December 2018) and winter (January 2019 to April 2019) terms, with 37 and 43 participants completing the study in the fall and winter terms, respectively. A total of 80 participants completed the 12-week trial (n=35 in the intervention group; n=45 in the control group; Figure 2).

**Figure 2 figure2:**
[figure not shown]
Flow diagram.

## Discussion

### Strengths

This study used a mixed methods design to capture both quantitative and qualitative findings from first-year university students’ experiences using MVP and is comprehensive in the variety of data captured. The MVP platform itself has a different approach than other web-based tools as it focuses on multiple pillars of health (mindfulness, nutrition, and physical activity), provides a comprehensive list of resources to its users, is developed by certified health professionals, and is guided by principles of CBT. In addition, the issues commonly experienced by university students were strongly considered in the development of MVP. For example, MVP delivered messages about stress management during key times in the academic term and guides to healthy eating on campus, further supporting healthy food choices.

### Limitations

Potential limitations of the study are related to the inclusion of only first-year university students and the monitoring of platform usage, which may have limited external validity. Attrition was higher in the group that received the intervention than in the control group, although platform usage data have not yet been analyzed. This suggests that systematic differences between groups should be examined in outcome analyses. Finally, all limitations will be examined and taken into account in the interpretation of the results.

### Conclusions

Preventative self-care is important for first-year university students who may not have established this skill and are simultaneously experiencing new stress and pressures of postsecondary education. Targets were obtained for the sample size. This study will determine whether the web-based platform has a direct impact on health and wellness among first-year university students and could become an important tool for virtual, preventative self-care delivery.

## Appendix

Multimedia Appendix 1 Screenshots of My Viva Plan.

Multimedia Appendix 2 Study timeline.

## Abbreviations

CBT: cognitive behavioral theory
FFMQ: Five Facet Mindfulness Questionnaire
HNRU: Human Nutrition Research Unit
MVP: My Viva Plan
NRF: nutrient rich food
REDCap: Research Electronic Data Capture
